### Data analysis

All analyses will be by intention to treat: patients will be analyzed according to the intervention arm for their site. At the individual level, the primary outcomes are dichotomous variables (e.g. 1 if the women received an uninterrupted supply of ART from initiation through delivery, 0 if not). For each study arm, these dichotomous outcomes can be summarized as proportions (the proportion pregnant women with HIV who receive an uninterrupted supply of ART from treatment initiation to delivery).

The analysis will begin with a simple comparison of the proportion of successes for each outcome (e.g. received an uninterrupted supply of ART from initiating to delivery) by study arm and crude risk ratios and 95% confidence intervals stratified by study arm will be reported. To estimate the risk difference between study arms, a linear probability model will be used with t-statistics and *p* values adjusted for the small number of clusters (study clinics). A linear probability model is appropriate for estimating impacts when treatment status is a binary (as in this study). [16] For inference, the *clustse* analysis in STATA will be used to adjust t-statistics and *p* values for the small number of clusters. *Clustse* implements the cluster-adjusted t-statistics described in [17] and wild cluster bootstrap procedure described in [18].

Because we will not be randomizing large numbers of patients during the intervention period, it is possible that some covariates may be imbalanced by study arm. To adjust for potential differences in such covariates, multivariate linear probability models will be used to estimate adjusted risk differences. Adjusted analyses will include covariates that are unevenly distributed across study groups for each outcome and could plausibly affect study outcomes. These include patient characteristics (e.g. age, weeks of gestation at first ANC visit, parity) and site characteristics. Statistical analyses will be completed using STATA. We will use similar analytic methods for analyzing secondary outcomes.

In addition, there is debate in the literature as to how the pair-matched design should be accounted for in the analysis to avoid bias. [19–22] To this end, supportive analyses will use alternative strategies to account for the pair-matched design in order to evaluate robustness of model-based estimators that do not explicitly account for the pair-matched design.

For the analysis of costs of implementing the EMMA intervention, we will use standard program costing analysis methods to assess the additional costs to the health facilities of providing the EMMA intervention [23–25]. Only program records are required for the cost analysis (e.g. training costs for Mentor Mothers, costs for phones and airtime, etc.). No human subject data are required for the evaluation of costs. See Additional file 5 for an overview of the main steps to be followed for completing the cost analysis.

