### Study population

The study population comprises all pregnant women with HIV presenting at a study site for their first antenatal care (ANC) visit. This includes women who are newly diagnosed with HIV as part of their first ANC visit (which is routine practice in the region and study sites) as well as pregnant women with HIV who are already on ART at their first visit for antenatal care.

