### Allocation to study arms

The 12 study sites were formed into six pairs, matched on observed characteristics including geographic location and number of HIV-infected pregnant women presenting for antenatal care (during 2016). Map 1 identifies the basic location for each study site, numbered from 1 to 12, which represents the order sites began enrolment (1 was first, 12 was last). The study site names by study arm are: (SOC Arm/EMMA Arm): 6 = Kapsabet District Hospital/1 = Kericho County Referral Hospital; 11 = Kapkatet District Hospital/4 = Transmara District Hospital; 8 = Kombewa County Hospital/5 = Nandi Hills District Hospital; 12 = Ratta Health Centre/3 = Bomet Health Centre; 2 = Longisa District Hospital/9 = Munyuanda Health Centre; 7 = Meteitei-Sub-district Hospital/10 = Bodi Health Centre. The largest sites were matched together and the study team tried to maintain regional balance between the six counties in which the study is being conducted.

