### Trial status

The current approved version of the protocol is Version 5.7, 6 March 2017.

Recruitment began on 17 March 2017. Enrollment was then put on hold during April–July 2017 pending PEPFAR assessment if research studies would continue to be funded.

Recruitment is expected to be complete in February 2018.

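### Adjustment covariates are picked by observed imbalance, per outcome and without a threshold; one fixed patient-level set should replace the rule

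*Protocol article*

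**What the plan says.** The Data analysis section starts with crude proportions and risk ratios and then gives an unadjusted effect model: "To estimate the risk difference between study arms, a linear probability model will be used with t-statistics", with inference suited to few clusters. Adjustment comes afterwards, because "it is possible that some covariates may be imbalanced by study arm". The selection rule is: "Adjusted analyses will include covariates that are unevenly distributed across study groups for each outcome and could plausibly affect study outcomes". The candidates are described as follows: "These include patient characteristics (e.g. age, weeks of gestation at first ANC visit, parity) and site characteristics". Nothing says how uneven a covariate must be, how many site-level terms may enter, or whether the adjusted or the unadjusted risk difference is the primary result.

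The Study population section enrols newly diagnosed women "as well as pregnant women with HIV who are already on ART at their first visit for antenatal care". P1 (Primary outcomes) counts uninterrupted ART supply from treatment initiation to delivery. The Allocation to study arms section lists the 12 clinics by pair and arm.

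**The concern.** Adjustment is worth making when a covariate predicts the outcome. Whether it happens to differ between arms is a poor guide: the rule can admit a weak predictor that is uneven and leave out a strong one that looks balanced. Without a threshold, two analysts could follow the text and fit different models.

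The words on each outcome add to this. They may mean separate selection for P1, P2 and P3, or imbalance judged among the women or infants who contribute to that outcome. The Sample size section expects transfers and pregnancy losses, so on the second reading the set is known only after follow-up.

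At stake are the error rate and precision of the adjusted risk difference, and whether the three primary results can be compared. With 12 clinics, open-ended use of site characteristics matters most, since each such term uses one of about 10 between-clinic degrees of freedom (12 − 2).

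**Working it through.** **Inputs from the protocol article (Sample size).** 12 clinics, 6 per arm; about 30 women per clinic, 180 per arm; ICC 0.04–0.05; two-sided 5% test; 25-point target. Table 1 reproduces. With continuity-corrected n per arm, cluster size is m = 2n(1−ρ)/(12−2nρ) and the design effect is 1+(m−1)ρ:
- n = 68, ρ = 0.04: m = 130.56/6.56 = 19.9, so 20; 1.76; 68 × 1.76 = 119.7, so 120 per arm.
- n = 70, ρ = 0.04: m = 134.4/6.4 = 21; 1.80; 126 per arm.
- n = 70, ρ = 0.05: m = 133/5 = 26.6, so 27; 2.30; 161 per arm.

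**Chance imbalance in ART status at entry.** The documents give no prevalence, covariate ICC or outcome gap. Assumed: prevalence p 0.3–0.5, covariate ICC 0–0.10, outcome gap 0.2–0.3 between women already on ART and newly diagnosed. SE = √[2p(1−p)/180 × (1+29·ICC)].
- Low end (p = 0.3, ICC 0): SE 0.048; 95% range ±9.5 points; shift in the risk difference 0.095 × 0.2 = 1.9 points.
- High end (p = 0.5, ICC 0.10): SE 0.104; ±20.4 points; shift 0.204 × 0.3 = 6.1 points.

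So a chance imbalance at the edge of its 95% range moves the estimate by about 2–6 points, against a 25-point target.

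**Null simulation of the rule.** 12 × 30, linear probability model, CR1 cluster standard errors, t with 10 df, 3000 runs per row. Assumed: outcome ICC 0.04, covariate ICC 0.05, and an individual-level p < 0.10 as the meaning of uneven. The fixed set is ART status plus three other patient-level covariates. The triggered set draws on those four and one site-level variable unrelated to the outcome.

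| Outcome gap | Type I: unadjusted | fixed | triggered | SD: unadjusted | fixed | triggered |
|---|---|---|---|---|---|---|
| 0.1 | 5.8% | 6.1% | 7.7% | 0.0768 | 0.0762 | 0.0818 |
| 0.2 | 5.9% | 6.3% | 7.6% | 0.0770 | 0.0755 | 0.0807 |
| 0.3 | 6.4% | 6.8% | 8.1% | 0.0784 | 0.0742 | 0.0809 |

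Triggered against fixed, the excess error is 1.6, 1.3 and 1.3 points. The variance ratios are (0.0818/0.0762)² = 1.15, (0.0807/0.0755)² = 1.14 and (0.0809/0.0742)² = 1.19. Monte Carlo error on one rate is about √(0.06 × 0.94/3000) = 0.4 points. With a true 25-point effect and a gap of 0.2 (2000 runs), power was 84.5% unadjusted, 86.8% fixed and 83.4% triggered.

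The source of the excess matters. When the same runs were repeated with the trigger confined to the four patient-level covariates, the excess type I error disappeared and the SD came back close to that of the fixed set. In this setting the cost therefore comes mainly from a site-level term entering through the rule.

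**Facility type, from the site list.** By name, SOC has 5 hospitals and 1 health centre; EMMA has 3 and 3. Two pairs set a hospital against a health centre, one of them "2 = Longisa District Hospital/9 = Munyuanda Health Centre". Under within-pair randomisation two discordant pairs fall the same way with probability 2/4 = 0.50. Correlation with arm: φ² = (5×3 − 1×3)²/(6×6×8×4) = 144/1152 = 0.125, so adding facility type multiplies the variance of the treatment effect by 1/(1−0.125) = 1.14 if it does not predict the outcome.

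**The case against.** The strongest reply is that the rule governs only a secondary layer. The unadjusted linear probability model comes first, does not depend on the rule, and nothing says the adjusted model replaces it. A condensed article also leaves covariate lists to a fuller document. The first part stands and limits the harm to the adjusted estimate. The second does not remove the point, because the article states a selection rule that a later plan would inherit.

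Several stronger readings are tempting and are not supported:
- *ART status is left out.* The patient covariates are introduced as examples, so it is unnamed, not excluded.
- *Visible site differences are known confounding.* Site characteristics are already eligible, the 5 versus 3 split is an ordinary chance result, and no figure shows that facility type predicts any outcome.
- *Calendar time confounds the comparison.* The site numbers give an order, "which represents the order sites began enrolment (1 was first, 12 was last", with mean rank 46/6 = 7.67 in SOC and 32/6 = 5.33 in EMMA (sign-flip p = 0.44). Start dates are not given. Recruitment opened on 17 March 2017, and "Enrollment was then put on hold during April–July 2017", so about two weeks preceded the hold and the text does not say which sites were open.
- *The model is chosen after outcomes are known.* Imbalance can be judged without outcome results; the wording is ambiguous.
- *The error rate is uncontrolled.* Reporting the most favourable subset of uneven covariates gave 9.4–11.3% in the simulation, but the protocol describes no such choice.

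**Conclusion.** The point holds for the adjusted risk difference. The rule as written is data-driven, has no threshold and permits three different models for three primary outcomes. Under the assumed inputs it costs about 1–2 points of type I error and 14–19% in variance compared with a fixed patient-level set, mainly by letting site-level terms in. These figures rest on an assumed p < 0.10 trigger, an assumed covariate ICC and outcome gap, a site-level variable with no effect on outcome, and CR1 standard errors in place of the planned clustse procedures; pairing was not modelled. The gain in precision from a fixed set over no adjustment is modest: 2% to 10% less variance, from (0.0762/0.0768)² = 0.98 to (0.0742/0.0784)² = 0.90. The unadjusted analysis is sound on this point, and the facility-type difference is a visible chance imbalance.

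**What to change.** Replace the imbalance rule with one covariate set, used for P1, P2 and P3 whatever the observed balance: ART status at first antenatal visit, gestational age at that visit, age and parity. State whether the unadjusted or the adjusted risk difference is primary; this does most to prevent selective emphasis.

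Allow at most one pre-specified site-level variable, such as facility type, preferably in a sensitivity analysis. It costs one between-clinic degree of freedom and, being correlated with arm, may inflate the treatment-effect variance by about 14% if it is not prognostic. Do not add a term for enrolment before or after the 2017 hold, since site start dates are not given.

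The change is one paragraph and leaves the sample size as it is. It assumes that ART status at entry can be taken from the routine records already being extracted. It should be made before outcome data are examined by arm.

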### Sample size

Each primary outcome is a proportion and the sample size (360 total, 180 per arm) was developed to be adequate to detect at least a 25 percentage-point improvement in each primary outcome between the two study groups (Arms SOC and SOC + EMMA). To begin, ignoring possible cluster effects, Table 1 first shows the sample size needed to detect a 0.25 proportional improvement between the two study groups, when the base proportion is in the range of 0.30–0.40 (with 5% significance, 80% power, assuming a two-sided test, using sampsi command in Stata 11). Baseline proportions > 0.4 have smaller estimated sample sizes than for 0.4, so they are not reported. Table 1 also shows how the sample size increases when possible clustering effects are included into the sample size calculation (using sampclus in Stata 11). With 12 possible clusters, and an intra-cluster correlation coefficient of 0.04 and 0.05, the sample size increases by 76–130% with six sites allocated to each study arm (and 20–27 patients per cluster).

**Table 1 Tab1:** Sample sizes to detect 25 percentage point difference in study arms (5% significance, 80% power)

SOC	SOC + EMMA	Random sample size SOC/SOC + EMA	Clusters (n)	Intra-cluster correlation (rho)	Total sample size	Per cluster	Implied design effect
0.30	0.55	68/68	12	0.04	120/120	20	1.76
0.40	0.65	70/70	12	0.04	126/126	21	1.80
0.40	0.65	70/70	12	0.05	161/161	27	2.30

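### The main model leaves out the factors the clinics were matched on, and the imbalance rule is unlikely to bring them back; entering 2016 clinic volume by prespecification would recover precision if volume is prognostic

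*Protocol article*

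**What the plan says.** Allocation to study arms (Protocol article) describes six pairs of clinics, "matched on observed characteristics including geographic location and number of HIV-infected pregnant women presenting for antenatal care" in 2016. It adds that the largest sites were put together and that balance across the six counties was attempted.

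Data analysis (same article) estimates the risk difference with a linear probability model, using t-statistics and p-values corrected for the small number of clusters. No pair term and no matching variable is named in that model. Adjusted models follow a selection rule: "Adjusted analyses will include covariates that are unevenly distributed across study groups for each outcome", with the further condition that the covariate could plausibly affect outcome. The candidates include patient characteristics and, in general terms, site characteristics.

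The last paragraph of the section acknowledges a debate on how pair matching should be analysed. It commits to supportive analyses that account for the pairs, as a robustness check on "model-based estimators that do not explicitly account for the pair-matched design".

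Sample size states that the trial is "adequate to detect at least a 25 percentage-point improvement in each primary outcome between the two study groups". Table 1 uses an ordinary intra-cluster correlation of 0.04 or 0.05 and assumes no gain from matching.

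**The concern.** Matching makes the two arms alike on the matching factors, so it reduces the true sampling variance of the arm difference when those factors predict outcome. A standard error that ignores the matching still counts that variance. The test then rejects less often than 5% under the null, the 95% interval over-covers, and power is left unused in a trial with only 12 clusters.

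The selection rule for the adjusted models pulls the same way. It asks for observed imbalance as well as prognostic plausibility. The better the matching has worked on volume, the less likely volume is to qualify, however prognostic it is. Whether it enters depends on how the data fall and not on a decision taken in advance.

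**Working it through.** **Inputs from the article.** 12 clinics, 6 per arm; two-sided 5%; 0.40 versus 0.65; ICC 0.05; 27 per clinic (largest row of Table 1), raised to about 30 for attrition. No matching correlation is given. Assumptions: equal clinic sizes, and t-tests on clinic means standing in for the planned small-cluster procedure.

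**1. Reproduce Table 1.** Two proportions with continuity correction give 70 per arm, so N = 140. Clinic size = N(1 − ρ)/(12 − Nρ) = 140 × 0.95/(12 − 7) = 26.6, so 27. Design effect = 1 + 26 × 0.05 = 2.30, and 70 × 2.30 = 161 per arm, as printed. Nothing in this chain uses the pairs.

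**2. Unadjusted analysis.** Variance of the difference = (0.40 × 0.60 + 0.65 × 0.35) × 2.30/(27 × 6) = 0.4675 × 2.30/162 = 0.00664, so the SE is 0.0815. With 10 df the half-width is 2.228 × 0.0815 = 0.1815 and the power 0.79.

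**3. What volume could remove.** The between-clinic part of the variance of a clinic mean is 0.05 × 27/2.30 = 0.587. If volume explains a share q of it, the residual variance is multiplied by 1 − 0.587q, and the test has 9 df (t = 2.262). The ratio of adjusted to unadjusted half-width, with volume perfectly balanced by arm, is (2.262/2.228) × √(1 − 0.587q):
- q = 0: 1.015 (1.5% wider)
- q = 0.25: 1.015 × 0.924 = 0.938
- q = 0.50: 1.015 × 0.841 = 0.853

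Break-even is at q = [1 − (2.228/2.262)²]/0.587 ≈ 0.05.

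**4. Simulation of clinic means (ICC 0.05, 27 per clinic).**
- Volume explains half: unadjusted type I error is about 2.6–3.1%, and power goes from about 0.79 to 0.87–0.88 with adjustment. One run gave coverage of 97.5% before and 95.2% after, and a full interval width falling from 0.366 to 0.314. A more favourable set-up gave power of 0.82 and 0.90.
- Volume explains a quarter: power from about 0.77 to 0.80–0.81.
- Volume explains nothing: power falls by one to two points (0.79 to 0.78 in one run, 0.77 to 0.75 in another).

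**5. If the prognosis lies in location.** Let matching explain half of the between-clinic variance in total. Split equally between volume and location, power goes from about 0.80 to 0.84 when volume alone is entered, and type I error stays below nominal at about 3.6%. If location carries all of it, power is 0.81 with or without volume.

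**6. Fully paired analysis, for comparison.** With six pairs it has 5 df (t = 2.571). Its interval is narrower only if the within-pair correlation of clinic proportions exceeds 1 − (2.228/2.571)² = 0.249, which is a correlation of true clinic effects of 0.249/0.587 = 0.42. At zero correlation it is 2.571/2.228 = 1.154 times as wide, with power 0.69 against 0.79.

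**The case against.** The strongest reply is that the article has already dealt with the matching: it recognises the debate, plans supportive pair-based analyses, and keeps a main model whose possible error is conservative. Most of that stands. Type I error is at or below 5%, and the unadjusted test keeps roughly its planned power even when matching is effective. A pair-based primary analysis would be a real trade-off at 5 df. The exact supportive strategy may properly be left to the analysis plan, so its not being named here is no fault.

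It also stands that the gain is not guaranteed. The article gives no evidence that volume predicts P1–P3, and volume is only one of the matching factors. The figures come from t-tests on clinic means, so they approximate the planned procedure.

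Three stronger readings are tempting, and the document does not support them:
- A reader might infer that the imbalance rule keeps the matching variables out. It does not: site characteristics are listed as candidates, and regional balance was only attempted, so location or volume could turn out uneven and enter.
- A reader might infer that the intervals are too wide as a matter of fact. That holds only if the matching factors are prognostic.
- A reader might infer that the power statement is wrong. It is not, because it claimed nothing from matching.

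What the reply does not reach is the one-covariate option. The fall from 10 to 5 df belongs to a fully paired analysis, whereas entering volume costs one df. Supportive analyses also leave the primary estimate and its interval as they are.

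**Conclusion.** The point holds as a conditional one about efficiency. The main model omits the factors used in the design, and the adjustment rule makes a well-balanced matching variable an unlikely entrant. If volume is prognostic, the trial forgoes precision that it could have at almost no cost: at ICC 0.05, about eight to nine points of power and an interval roughly 14–15% narrower if volume explains half of the between-clinic variance, and three to four points of power if it explains a quarter. If volume explains nothing, adjustment loses one to two points. If location carries the prognosis, adjustment for volume does little or nothing. These shares are assumptions; the article offers no data to choose among them. Neither the validity of the test nor the sample-size statement is in question.

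**What to change.** In Data analysis, state that the primary linear probability model for P1–P3 includes each clinic's 2016 number of HIV-positive antenatal clients (for example on the log scale) as a fixed covariate, whatever the observed balance. Volume then no longer depends on the imbalance rule. Keep the pair-based analyses as supportive.

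The cost is wording only, since the 2016 counts were already used to form the pairs. The statistical price is one degree of freedom (10 to 9), or about one to two points of power if volume is unrelated to outcome. The change does not recover precision that lies in location.

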### Study monitoring

All of the patient-level data used for this study will be extracted from information routinely collected at the study sites and contained in patient medical records (paper files for the mother’s visit extraction form and the mother-infant form; electronic file for the Mentor Mother/Patient Encounter).

As these forms are completed over time based on the study schedule, they will be checked for completeness by the study coordinator. If any changes to forms are made, the original data will be left and crossed out and the corrected data will be written next to it with a signature and date of the person who made the change. The Study Coordinator will provide monthly updates on study enrollment numbers to the PI for monitoring enrollment progress.

Given the largely observational nature of this study, monitoring will focus upon, but not be limited to, informed consent, patient confidentiality, regulatory components (e.g. IRB approvals), and IRB reports. The PI will conduct monitoring activities every six months, in which an experienced study coordinator and data manager working with Walter Reed/KEMRI program in Kericho will review 100% of informed consents and a 10% sample of all newly completed forms and entered data since the last monitoring visit and compare to original medical records. If any issues are found during regulatory monitoring activities, a one-time monitoring visit will be done within a period of three months and staff will be retrained. For this minimal risk study addressing behavioral and staff management issues, a data monitoring committee was not organized [26].

